**Fig. 3 Fig3:**
[figure not shown]
Standardised transvaginal ultrasound evaluation of a niche in the non-pregnant uterus. **a**. Measured in the transversal plane: niche width (1); **b**. Measured in the sagittal plane: niche length (2), niche depth (from cervical canal until apex of the niche) (3), residual myometrium thickness (from deepest part of the niche until the serosa) (4), adjacent myometrium thickness (myometrium thickness close to base of the niche) (5), distance from apex of the niche to vesico-vaginal fold (see **c**) (6); **c**. Measuring the niche relatively to the vesico-vaginal fold in the sagittal plane: positive value (green arrow, in mm) or negative value (red arrow, in mm)

#### Data niche evaluation

Results of the TVUS and GIS or SIS, performed three months after CS, will be registered. Women will not receive information regarding the presence of a niche, since it has no clinical consequences so shortly after CS and this may influence the answers given in the questionnaires. Other important abnormalities visualised by ultrasound will be reported as usual.

### Statistical issues

#### Sample size calculation

We use a superiority design since we expect double-layer closure to be favourable. Literature for making reliable estimations on postmenstrual spotting in relation to niches is scarce. We have used baseline data from the HysNiche [19] and LapNiche [15] study. We estimate the mean number of spotting days to be 3.5 days/month in the total group. We consider a 15% reduction in the mean number of spotting days clinically relevant, which is 0.5 day/month reduction. Assuming a standard deviation (SD) of 3.4 and a two-sided significance level of 5%, a total of 1488 women need to be included to achieve a power of 80%. Increasing the sample size to take into account 35% of women unevaluable (due to drop-out, non-response or amenorrhoea) for the primary outcome, 2290 women need to be included.

#### Data-analysis

Data-analysis will be performed according to the intention to treat principle and additional per protocol analyses will be performed. A test will be considered statistically significant when the two-sided test shows a *p*-value < 0.05. Baseline characteristics will be presented using percentages, means with SD and 95% CI or medians with interquartile ranges (IQR), where appropriate.

The primary outcome, number of days of postmenstrual spotting, will be presented for both groups as mean with SD or median with IQR, and presented in a Box-Whisker graph to show the distribution. Differences in primary outcome between the groups will be tested using the independent t-test in case of normal distribution (possible after transformation of the outcome) or Mann-Whitney U test. An adjusted analysis will be performed using linear regression analysis in which we adjust for factors on which randomisation was stratified and for baseline factors on which relevant differences are observed despite randomisation.

Dichotomous secondary outcomes will be presented as percentages and RR with corresponding 95% CI. *P*-values will be calculated using the chi-square test or, if the expected count for at least one cell is below 5, using the Fisher exact test. Normally distributed continuous variables will be presented as means with SD, and differences between the groups will be calculated with an independent t-test. Non-normally distributed continuous variables will be presented as medians with IQR and differences between the groups will be calculated with Mann-Whitney U test. The questionnaires will be analysed using the appropriate algorithms and usual presentation methods (FSFI, EQ-5D-5L, SF36, PROMIS SF8a, iMCQ, iPCQ).

Comparison of primary outcome between women receiving single- and double-layer closure will be done as secondary analyses within each of the following subgroups separately:Planned (without labour) or unplanned (in labour) CSEmergency CS or notPreterm (< 37 weeks gestational age) or term (≥ 37 week gestational age) CSPresence (> 3cm) or absence (≤ 3cm) of dilatationPlacenta praevia or notPresence or absence of specific maternal morbidity (e.g. diabetes, pre-eclampsia, haemolysis/elevated liver enzymes/low platelet count (HELLP) syndrome, immunodeficient women)Singleton versus twin pregnancyNatural cycle or hormonally induced withdrawal bleeding

Within the single-layer group (control group) we will compare the primary outcome between women in whom endometrial saving technique (split thickness) was applied and women in whom an endometrial saving technique was not applied (full thickness).

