### Recruitment and randomisation

Eligible women will be asked by a gynaecologist, resident, clinical midwife or research nurse to participate in the trial when they undergo a planned CS. Eligible women who are planned to undergo a vaginal delivery will also be informed about this study during pregnancy in case they need an unplanned CS. Furthermore, women during induced labour and women receiving adequate therapy for pain during labour, will be asked to participate in case a CS is needed during labour for any indication.

When the decision of a CS is made and all selection criteria are met, women will be randomly allocated to single-layer (control group) or double-layer (intervention group) closure (1:1) (see Fig. 1). Randomisation will be performed using a web-based application ALEA 2.2 which displays a computer-generated random number, managed by the Clinical Research Unit of the Amsterdam UMC - location AMC. We will use a permuted block-design, stratified for recruiting centres and for planned or unplanned CS. All women that decline to participate will be registered anonymously in order to record the number and reason for refusal. Subjects who withdraw from this study will not be replaced. 

Gynaecologists, residents, clinical midwives or research nurses enrol participants and assign them to the intervention. The CS will be performed by either a gynaecologist, a resident supervised by a gynaecologist or by a resident that is authorised to perform CSs without supervision. Participants and sonographers will be blinded for the closure technique. If operative reintervention after CS is needed and the gynaecologist that performs the reintervention needs to know the closure technique that the participant was assigned to, unblinding is possible through the logistic trial coordinator. We expect this situation to occur very infrequently.

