#### Collection of baseline characteristics and patient reported outcomes

Baseline characteristics will be collected through a digital questionnaire at 2–4 weeks after caesarean section, sent to the e-mail address of participants. Since we will also include unplanned CSs, we decided that it is not possible for all participants to answer questions regarding baseline characteristics before the operation. Baseline parameters include maternal age, body mass index, social economic status, smoking habit, medical and obstetric history, gestational age and previous vaginal deliveries, all reported by the participant. We expect that the impact of niche related symptoms such as postmenstrual spotting on daily activities and sexual behaviour may be influenced by ethnic background and religion, therefore we will also register these characteristics. At three months, nine months and three years follow-up, again digital questionnaires will be sent to participants to assess the primary and secondary outcomes (see Fig. 1). At nine months, we ask participants record their exact menstrual and spotting pattern, if any, in an adjusted menstruation score chart. [33] Reminders for all questionnaires will be sent every two weeks, with a maximum of three times. When no response is given after the reminders, research nurses from participating centres will be asked to call the participant.

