#### Economic evaluation

The economic evaluation will be performed alongside the RCT from a societal perspective. Both a cost-effectiveness and cost-utility analysis will be performed with a time horizon of nine months to relate the difference in societal and healthcare costs between double-layer and single-layer unlocked uterine closure during a CS to the difference in clinical effects. Healthcare costs include costs of primary and secondary care, complementary care and home care. Costs in other sectors include presence and absence from paid and unpaid work. The friction cost approach will be used to estimate indirect costs. For the valuation of health care utilization standard prices published in the Dutch Costing guidelines will be used. [34] Medication use will be valued using prices of the Royal Dutch Society for Pharmacy.

Societal costs will be related to the following effect measures in the economic evaluation: days with postmenstrual spotting and quality-adjusted life-years (QALYs) based on the Dutch tariff for the EuroQol (EQ-5D-5L). [27, 28, 35]

We hypothesise that double-layer uterine closure will reduce postmenstrual spotting and related consultations for gynaecological or fertility related problems and applied therapies, and as a consequence that it will be cost-effective in comparison with single-layer uterine closure.

The analysis will be done according to the intention to treat principle. Missing costs and effect data will be imputed using multiple imputation. Incremental cost-effectiveness ratios (ICERs) will be calculated by dividing the difference in mean total costs between the treatment groups by the difference in mean effects. Bootstrapping with 5000 replications will be used to estimate 95% CI around cost differences and the uncertainty surrounding the ICERs. Uncertainty surrounding the ICERs will be graphically presented on cost-effectiveness planes. Cost-effectiveness acceptability curves showing the probability that double-layer uterine closure is cost-effective in comparison with single-layer uterine closure for a range of different ceiling ratios will also be estimated. Adjustment for confounders and effect modifiers will be done if necessary. [36]

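### The primary test leaves out the randomisation strata, and the adjusted model adds covariates because they look imbalanced: a modest loss of precision and a data-dependent secondary model, not an inflated error rate

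*Protocol article*

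**What the plan says.** Under Recruitment and randomisation, the protocol article specifies a "permuted block-design, stratified for recruiting centres and for planned or unplanned CS".

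Under Data-analysis, the difference in the primary outcome (days of postmenstrual spotting in one cycle at nine months) is to be "tested using the independent t-test in case of normal distribution (possible after transformation of the outcome) or Mann-Whitney U test". Neither test uses centre or type of caesarean section. The next sentence adds a linear regression that will "adjust for factors on which randomisation was stratified and for baseline factors on which relevant differences are observed despite randomisation".

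The article gives no threshold for a relevant difference and does not name the factors to which the rule applies. It does not say how the adjusted result ranks against the unadjusted one if they disagree. The baseline items listed under Collection of baseline characteristics and patient reported outcomes run from maternal age and body mass index to obstetric history and previous vaginal deliveries, so the pool of candidates is wide.

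**The concern.** There are two separate weaknesses.

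First, stratified allocation balances the arms on the strata and so removes between-stratum variation from the treatment comparison. An unadjusted test still counts that variation in its standard error. To the extent that the strata predict spotting, the standard error is too large, the interval too wide and the test less powerful than the design allows.

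Second, differences between randomised arms at baseline arise by chance. The size of such a difference does not show whether a factor predicts the outcome. A rule that adjusts where a difference is seen can bring in irrelevant factors and leave out strong predictors that happen to be balanced. It also means that the adjusted model cannot be written down until the arms have been compared. This is more than a detail left open for the statistical analysis plan: the article states the selection rule, and a later covariate list would have to replace it.

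**Working it through.** **Inputs.** From Sample size calculation: difference 0.5 day, SD 3.4, two-sided 5%, power 80%, 1488 evaluable women, 35% unevaluable, 2290 randomised. Allocation is 1:1 (Recruitment and randomisation). The share of outcome variance explained by the strata, R², is not given and is assumed to be 0.02, 0.05 or 0.10.

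**The plan's own figure.** n per arm = 2 × (3.4/0.5)² × (1.960 + 0.842)² = 725.9, so 726 per arm and 1452 in total. That is 2.4% below the stated 1488. Inflation: 1488/0.65 = 2289.2, rounded up to 2290, which matches. The sample size rests on an unadjusted comparison of two means and is not in error.

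**Effect of leaving the strata out.** With the arms balanced within strata, the true standard error is the nominal one times √(1 − R²). Hence:

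- relative width of the unadjusted interval: 1/√(1 − R²)
- true type I error of the unadjusted test: 2 × [1 − Φ(1.960/√(1 − R²))]
- power of the unadjusted test: Φ(0.842/√(1 − R²))
- power of the adjusted test: Φ(2.802/√(1 − R²) − 1.960)

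| Assumed R² | Interval too wide by | True type I error, unadjusted | Power, unadjusted | Power, adjusted | Gain (points) |
|---|---|---|---|---|---|
| 0 | 0% | 5.0% | 80.0% | 80.0% | 0 |
| 0.02 | 1.0% | 4.8% | 80.2% | 80.8% | 0.5 |
| 0.05 | 2.6% | 4.4% | 80.6% | 82.0% | 1.4 |
| 0.10 | 5.4% | 3.9% | 81.3% | 84.0% | 2.7 |

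Gains are taken before rounding. The comparator is the unadjusted test under the same stratified allocation, not a flat 80%. At 744 per arm (1488/2), the gains are almost the same: 0.5, 1.3 and 2.6 points. At R² = 0.01 the gain is about 0.3 points.

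**Allowing for the expected 35% loss.** If loss is random, it partly undoes the balance, and the true variance factor becomes 1 − 0.65 × R². The type I error of the unadjusted test is then about 4.6% at R² = 0.05 and 4.3% at 0.10. The gains from adjustment become about 1.6 and 3.2 points. The interval widths in the table are therefore upper limits for how conservative the unadjusted interval is.

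**Effect of selecting on imbalance.** A simulation used 1488 women, 4000 replicates and eight independent covariates. Each covariate entered the model only if its standardised difference exceeded about 0.10 (roughly p < 0.05). The number of covariates, their strength and the threshold are all assumptions.

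| Each covariate's R² | Type I error, selected on imbalance | Type I error, better of unadjusted and selected | Power, unadjusted | Power, selected on imbalance | Power, all eight fixed in advance |
|---|---|---|---|---|---|
| 0.01 | 0.047 | 0.053 | 81.2% | 81.0% | 83.9% |
| 0.03 | 0.041 | 0.055 | 79.6% | 81.7% | 90.1% |

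The Monte Carlo standard error of the type I figures is about 0.003. The selection rule is slightly conservative, and even reporting the better of the two p-values moves the error rate little. What the rule gives up is most of the power that prognostic covariates fixed in advance would bring.

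**The case against.** The strongest reply is that the primary conclusion does not rest on the data-driven model. The article first states how the primary outcome is tested and then adds the adjusted analysis. The primary test is valid and errs on the safe side, and the adjusted model already contains the strata, so only its last clause depends on the data. All of this stands, and it limits the point to efficiency and pre-specification. It does not defend the imbalance clause. Nor does it give a reason to leave out strata that are known for every woman at randomisation.

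A reader might infer more than the article supports:

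- **That the nominal error rate is invalidated.** The simulated departures above are small, and selection alone moves the rate downwards.
- **That chance imbalance is itself the harm.** With 8 to 12 independent factors, at least one reaches p < 0.05 in 34% to 46% of trials (1 − 0.95⁸ and 1 − 0.95¹²). This is neither an error rate nor a bias, and the article does not define a relevant difference by a significance test.
- **That covariates are chosen after unblinding.** No timing is stated. The choice depends on the data even if the arm labels are masked.
- **That women who miss the baseline questionnaire drop out of the adjusted model.** The article states no complete-case rule, and the handling of missing covariates is ordinary content of a statistical analysis plan.
- **That the economic evaluation has the same defect.** Its sentence, "Adjustment for confounders and effect modifiers will be done if necessary", is a condensed remark about a different analysis, and a covariate list for it may properly sit elsewhere.

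One technical reservation also stands. The power figures are normal-theory results for a comparison of means and do not cover the Mann-Whitney branch, so the fix must deal with skewness.

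**Conclusion.** The point holds as a modest improvement that is nearly free. The primary test ignores the factors used to stratify randomisation. It stays valid but is mildly conservative, and adjustment would gain about 0.5, 1.4 or 2.7 points of power at an assumed R² of 0.02, 0.05 or 0.10, and next to nothing if the strata hardly predict spotting. The rule for adding covariates on observed imbalance makes the adjusted model data-dependent and aims at the wrong property of a covariate, without material inflation of type I error. The sizes rest on assumed R² values, normal theory, and either full balance within strata or random loss of 35%.

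**What to change.** - Make linear regression of spotting days on arm, planned or unplanned caesarean section, and centre the primary analysis, reporting the adjusted mean difference. Pool small centres or fit centre as a random effect. This estimates the quantity on which the sample size is based, a difference in means.
- If the outcome is skewed, use a robust or bootstrap standard error.
- Keep the unadjusted t-test or Mann-Whitney U test as a sensitivity analysis.
- Delete the second half of the adjustment rule, on baseline factors with observed differences.
- If further covariates are wanted, choose them for expected prognostic value and name them before any data are compared by arm.

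The cost is a change of wording. The strata are recorded at randomisation, and no new data or change in sample size is needed.

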### Outcome measures

#### Primary outcome measure

The primary outcome is the number of days of postmenstrual spotting during one cycle at nine months after CS. We defined postmenstrual spotting as brownish discharge for more than two days at the end of the menstruation, with a total duration (menstruation and spotting) of more than seven days, or intermenstrual blood loss that starts after the end of the menstruation. [8] The number of days of postmenstrual spotting will be counted as follows: days with brownish discharge (> two days) when the total duration of menstruation and spotting exceeds seven days + number of days with intermenstrual blood loss. Amenorrhoeic women, due to lactation, medication or other diseases, will not be evaluable for the primary outcome and will be left out of this analysis.

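### Subgroup effects are to be judged by separate within-level comparisons, with no interaction test, and one of the eight subgroup factors is determined only after randomisation

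*Protocol article*

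**What the plan says.** The Data-analysis section fixes the subgroup method: "Comparison of primary outcome between women receiving single- and double-layer closure will be done as secondary analyses within each of the following subgroups separately". Eight factors follow:

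- planned or unplanned CS
- emergency or not
- preterm or term
- dilatation above 3 cm or not
- placenta praevia or not
- specific maternal morbidity or not (an open list of examples)
- singleton or twins
- natural cycle or hormonally induced bleed

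The same section gives one general rule, without exceptions: "A test will be considered statistically significant when the two-sided test shows" p below 0.05. It names no interaction test. Effect modifiers are mentioned only in the Economic evaluation section.

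On timing, Recruitment and randomisation says: "When the decision of a CS is made and all selection criteria are met, women will be randomly allocated". The primary outcome is the "number of days of postmenstrual spotting during one cycle at nine months after CS".

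**The concern.** A subgroup analysis asks whether the effect of closure technique differs between kinds of women. A test inside one level asks something else: whether there is evidence of an effect in that level alone. The answer depends heavily on how many women the level contains. The trial is sized for the whole evaluable sample, so every level is underpowered. One significant level beside one non-significant level is then an ordinary result even when the effect is identical in both, and it is easily read as effect modification.

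The cycle-type factor raises a second issue. The other seven factors are in essence settled before the uterus is closed, so the arm cannot change them. Cycle type describes the bleed assessed nine months later. The Secondary outcome measures at short-term section counts therapy for gynaecological symptoms as an outcome, and the Economic evaluation section hypothesises that double-layer closure will reduce such therapies. If that therapy includes hormones, membership of this subgroup may depend on the arm, and the women compared within a level would no longer be groups formed by randomisation.

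**Working it through.** **Inputs from the document.** Sample size calculation: difference 0.5 day, SD 3.4, "two-sided significance level of 5"%, and "a total of 1488 women need to be included to achieve a power of 80"%; 35% unevaluable; 2290 randomised. Recruitment and randomisation: 1:1 allocation. Data-analysis: eight two-level factors, 8 × 2 = 16 strata, a minimum because the morbidity list is open. The level shares are **assumed**.

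**Plan's own figure.** n per arm = 2 × 3.4² × (1.960 + 0.842)² / 0.5² ≈ 726, so 1452 in total. The stated 1488 is 2.5% higher, which is close enough. 1488 / 0.65 = 2289.2, which rounds up to the stated 2290.

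**Discordance under a uniform true effect.** At 80% overall power the non-centrality is 1.960 + 0.842 = 2.80. In a level holding a fraction f of the women it is 2.80 × √f, and the power is about Φ(2.80√f − 1.96). The levels contain different women, so

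P(one significant, the other not) = p₁(1 − p₂) + p₂(1 − p₁).

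| Assumed split | Power, smaller level | Power, larger level | Discordant |
|---|---|---|---|
| 50:50 | 51% | 51% | 50% |
| 30:70 | 34% | 65% | 55% |
| 20:80 | 24% | 71% | 61% |

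With 744 per arm, a 0.5-day effect and SD 3.4, overall power is 81% and power per half is 52%. The discordance figures stay at 50%, 55% and 61%. They rise to 69% for 10:90 and 77% for 2:98.

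**Same situation with an interaction test.** If the effect is uniform, a 5% interaction test wrongly signals a difference in 5% of trials per factor, whatever the split. Over several factors, treated as independent: eight tests give 1 − 0.95⁸ = 34%; seven give 1 − 0.95⁷ = 30%. Simulation of eight mutually independent factors gave 32% to 35%. An exploratory label is therefore still needed.

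**Power of the interaction test.** Overall SE = 2 × 3.4 / √1488 = 0.176. Interaction SE = 0.176 / √(f(1 − f)), which is 0.353 at 50:50 and 0.441 at 20:80. The difference in effect detectable with 80% power is 2.80 × SE: about 1.0 day at 50:50 and 1.2 days at 20:80, against a planned overall effect of 0.5 day.

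**Timing of the cycle factor.** Randomisation takes place at the decision for CS; the cycle is assessed nine months after it. The factor is therefore determined after randomisation. No arithmetic applies, because the document gives no rate of hormone use and no reasons for it by arm.

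**The case against.** The strongest reply is that these analyses are labelled secondary, that the article nowhere says a significant level beside a non-significant one will be read as a difference, and that interaction tests and multiplicity handling may stand in an analysis plan not shown here. Much of this is fair. The primary test and main conclusion do not depend on the subgroups, and a recommendation for one kind of CS only would be a reader's step, not one the article announces. But the text does more than stay silent: it commits to comparing the arms separately within levels. Followed as written, that method cannot answer the question a subgroup analysis poses.

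Some stronger readings are tempting and are not supported:

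- **Treatment received.** A reader might take the reference to women receiving each closure as an as-treated comparison. The section opens with intention to treat, so this is loose wording.
- **A 56% chance of a false positive somewhere.** That is 1 − 0.95¹⁶ and needs 16 independent tests. All factors re-cut the same women. Simulations under no effect gave about 37% to 41% for at least one significant stratum, but these rest on assumed shares and mutually independent factors. Planned CS, emergency and dilatation clearly overlap, which would lower the figure somewhat.
- **Demonstrated bias in the cycle split.** The route through symptom treatment is plausible on the article's own hypothesis. Nothing shows that it operates or differs by arm, and the split has a legitimate descriptive use.

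A last objection concerns the remedy: the primary test is a t-test or Mann-Whitney U test, so there is no primary regression model to hold an interaction term. That is correct. The term belongs in the adjusted linear regression that the section also plans.

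**Conclusion.** The point holds as a recommendation about secondary analyses. The stated method invites false contrasts between levels: with the effect identical everywhere and the planned 80% overall power, about half of trials would show one for an evenly split factor, and about 61% for a 20:80 factor, against 5% per factor with an interaction test. This rests on assumed splits and on a true effect equal to the planned one; the conclusion is the same across the range shown. For the cycle-type factor, the timing after randomisation is clear from the text, while the bias is potential only. A reader should not infer that the primary result is compromised.

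**What to change.** Revise the subgroup paragraph before unblinding:

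1. For each of the seven factors fixed at or before the CS, fit one treatment-by-subgroup interaction, with the factor's main effect, in the adjusted linear regression already planned, by randomised arm.
2. Report the effect in each level with its 95% CI, without within-level significance tests.
3. Label all subgroup results exploratory.
4. Report the natural versus hormonally induced cycle split descriptively only.
5. Replace the wording about closure received with closure allocated.

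The cost is wording and a few model terms, with no new data or participants. The downside is that interaction tests have low power: only differences in effect of about 1 day or more would be found reliably. That is an honest statement of what this sample can say about subgroups.
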